# A Comparison of Ultrasound Guided Curettage With and Without Uterine Artery Embolization on Controlling Intraoperative Blood Loss for a Cesarean Scar Pregnancy Treatment: Study Protocol for a Randomized Clinical Trial

**DOI:** 10.3389/fendo.2021.651273

**Published:** 2021-06-07

**Keywords:** randomized clinical trial, cesarean scar pregnancy, uterine artery embolization, intraoperative blood loss, quantitative risk-scoring system

## Abstract

**Introduction:**

Cesarean scar pregnancy affects 6% of all ectopic pregnancies in women with prior cesarean section, and there is currently no consensus on the optimal treatment. Options of surgical treatment have a risk of intraoperative blood loss; therefore, uterine artery embolization (UAE) has been considered as an option of reducing intraoperative blood loss. However, UAE may be overused in clinical practice, especially in China. We present this protocol for a randomized clinical trial investigating the necessity of performing UAE for cesarean scar pregnancy, in combination with surgical suction curettage, taking into account the different subtypes of cesarean scar pregnancy. We recently developed a risk-scoring system (QRS) to estimate intraoperative blood loss, with 93.8% sensitivity and 6.3% false negative. Through this randomized clinical trial, we will retrospectively validate the QRS score on predicting intraoperative blood loss.

**Methods and Analysis:**

We propose undertaking a randomized clinical trial sequentially recruiting 200 patients. All the patients will randomly receive ultrasound guided curettage with or without UAE. Data on the subtypes of cesarean scar pregnancy (Types 1 and II and III) detected by ultrasound will be collected before operation. The score on estimating intraoperative blood loss assessed by our recently developed quantitative risk-scoring system (QRS) will be collected before the operation. We will primarily compare the duration of the operation, intraoperative blood loss, and complications between the two groups. We will also retrospectively analyze the association of subtypes of cesarean scar pregnancy and the options of treatment and validate the QRS score. Outcomes of subsequent pregnancy within the 2-year follow-up will be secondary outcomes.

**Trial Registration Number:**

[website], identifier ChiCTR2100041654.

## Introduction

Cesarean scar pregnancy is a rare type of ectopic pregnancy implanted in the myometrium at the site of a previous cesarean section scar. Although the estimated incidence is 0.04 to 0.05% of pregnancies worldwide (1), the number of reported cases has significantly increased in the last decade. Given the risk of this life-threatening complication, management of cesarean scar pregnancy is becoming another challenge for gynecologists.

There is currently no agreement on the most optimal management of cesarean scar pregnancy. Lack of clinical trial studies with a large enough sample size to compare the advantages among the treatment options (2, 3) results in the majority of studies on cesarean scar pregnancy being reported in literature as case series (4). This consequently results in that the optimal treatment is likely based on the individual case (4, 5) and the hospital’s individual protocol or gynecologists’ experiences. Although medical treatment with systemic or local methotrexate (MTX) is popular in western countries because of the lower risk for blood loss, nearly 50% of cases diagnosed in the first trimester of pregnancy often receive surgical treatment (1). Surgical treatment includes transvaginal or hysteroscopic or laparoscopic resection and uterine artery embolization (UAE) combined with or without hysteroscopic resection or curettage (4, 6, 7).

Increasing evidence indicated that cesarean scar pregnancy is a precursor of abnormally adherent placenta later in pregnancy (8), suggesting an increased risk of a severe hemorrhage or hysterectomy could occur at the time of operation/delivery (1, 8). Although UAE can reduce the risk of intraoperative blood loss and shorten the time for *β*-hCG (human chorionic gonadotropin) normalization and hospital stay and is a safe option for caesarean scar pregnancy treatment (9, 10), a recent retrospective study reported that the necessity of UAE is low (11), suggesting that UAE may be overused in clinical practice, in particular in China (4). A recent retrospective study also reported that simple surgical suction curettage under ultrasound guidance for the treatment of cesarean scar pregnancy in a lower uterine segment is effective and safe with less intraoperative blood loss (12).

Pre-assessment of blood loss is very important to gynecologists. Our recent study reported that gestational age of cesarean scar pregnancy and blood flow around the site of the gestational sac detected by ultrasound are risk factors for potential intraoperative blood loss (13). We then developed a risk-scoring system (**Table 1**) to estimate intraoperative blood loss, and we found that women with a total score higher than three have a risk for intraoperative blood loss (13). A previous study also used a color Doppler scoring system to estimate intraoperative blood loss, according to vascularization of the pregnancy, and it indicated that women with a higher score have a higher risk of intraoperative blood loss (12).

**Table 1 T1:** Risk-scoring system for the prediction of compression hemostasis requirement.

Variable	Score
Vascularity around the gestational sac*	
No obvious blood flow	0
Sparse or sporadic blood flow	1
Vessel looks like short-columnar pattern	2
Vessel looks cord-like pattern	3
Massive blood flow or arteriovenous fistula	4
Pregnancy duration	
≤40 days	0
41–50 days	1
>50 days	2

*As demonstrated on a color Doppler ultrasonography.

There is currently no randomized clinical trial to compare the intraoperative blood loss and postoperative outcomes by surgical treatment such as ultrasound guided curettage with or without UAE in women with cesarean scar pregnancy. Therefore, we will run a randomized clinical trial to primarily investigate whether UAE is overused in controlling intraoperative blood loss in clinical practice. We recently established a risk-scoring system (QRS) to estimate intraoperative blood loss (13), and we will then retrospectively validate the role of QRS in estimating intraoperative blood loss in this randomized clinical trial with a relatively large sample size. Recently a number of studies reported potential complications in a subsequent pregnancy in women who received surgical treatment (14). Whether the complications in a subsequent pregnancy are related to the options of the previous treatment is unknown. Therefore, the secondary measurement of this randomized clinical trial is to follow up the outcomes in a subsequent pregnancy in women treated by ultrasound guided curettage with or without UAE.

## Methods

### Study Design and Ethics

The randomized clinical trial will be conducted in a single university hospital specialized in Obstetrics and Gynaecology in China. Our tertiary hospital is the largest Women’s hospital in China. We have approximately 150 cases a year. This randomized clinical trial has been approved by The Hospital of Obstetrics & Gynaecology, Fudan University of China (Reference number KYY2020-185, and Trial registration number: ChiCTR2100041654).

### Participants

#### Sample Size Calculation

The sample size calculation was based on the reduction of the proportion of cases who lost more than 300 ml of blood during operation. Our recent study (15) showed intraoperative blood loss with a mean of 184 ml and a standard deviation (SD) of 313 ml. Converting to a Z-score, about 35% of cases would have more than 300 ml of intraoperative blood loss. With 90% power at the 5% significance level, recruiting 200 cases in total, we will be able to detect a difference of 20% between two groups.

Therefore, in this randomized clinical trial, 200 women newly diagnosed with cesarean scar pregnancy will be recruited within three years and equally divided into two groups.

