### Primary Outcomes

Comparisons of duration of operation, intraoperative blood loss and intraoperative complications between treatments by ultrasound guided suction curettage with or without UAE.The numbers of cases that receive emergency hysteroscopic and/or laparoscopic resection.Retrospectively analyze the intraoperative blood loss, taking into account the subtypes of cesarean scar pregnancy.Retrospectively validate the QRS score to predict intraoperative blood loss.

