### Statistical Analysis

All the data will be expressed as mean and SD. Student t-test or ANOVA will be performed when appropriate using Prism software version 8.4. Two side p value of less than 0.05 will be considered statistically significant.

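### The 90% power is for a comparison of proportions above 300 ml, but the outcome list gives no threshold and the stated tests compare means, so the power for the stated analysis is unknown

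*Protocol article*

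**What the plan says.** Three sections of the protocol article bear on this.

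- **Sample Size Calculation.** The endpoint is binary: "The sample size calculation was based on the reduction of the proportion of cases who lost more than 300 ml of blood during operation". The reference rate comes from an earlier study's "intraoperative blood loss with a mean of 184 ml and a standard deviation (SD) of 313 ml", from which the authors conclude: "Converting to a Z-score, about 35% of cases would have more than 300 ml of intraoperative blood loss". The claim is then "With 90% power at the 5% significance level, recruiting 200 cases in total, we will be able to detect a difference of 20% between two" arms, with "200 women newly diagnosed with cesarean scar pregnancy will be recruited within three years and equally divided into two groups".
- **Primary Outcomes.** The first item reads "Comparisons of duration of operation, intraoperative blood loss and intraoperative complications between treatments". Blood loss is named without a cut-off. The other items are the number of emergency resections, an analysis by subtype and validation of the QRS score. The Secondary Outcomes section has no blood loss threshold either.
- **Statistical Analysis.** All data are to be summarised by mean and SD. The tests are given as "Student t-test or ANOVA will be performed when appropriate using Prism software version 8.4", and "Two side p value of less than 0.05 will be considered statistically significant". No test for a proportion is named.

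**The concern.** The quantity that justifies 200 women is a proportion. The quantity that the outcome and analysis sections describe is a mean in millilitres. A reader who follows the article as written would compare means, for which it gives neither a target difference nor a power.

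This matters because the trial asks whether embolization is overused. A non-significant t-test could be read as evidence that embolization is unnecessary, with the 90% figure cited in support, although that figure describes a different test. Because the 300 ml comparison is not a listed outcome, it could also be dropped once the data are known without any departure from the outcome list.

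**Working it through.** **Inputs.** From Sample Size Calculation: mean 184 ml, SD 313 ml, cut-off 300 ml, reference rate about 35%, difference 20%, power 90%, 200 women split equally (100 per arm). From Statistical Analysis: two-sided 0.05. The protocol gives no target difference in means, so the mean differences in steps 4 and 5 are assumptions.

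**1. The 35%.** z = (300 − 184)/313 = 0.371, and the upper normal tail is 35.5%. This agrees with the protocol.

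**2. The 200.** Take 35% against 15%, with pooled proportion 0.25.

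- n per arm = [1.960 × √(2 × 0.25 × 0.75) + 1.282 × √(0.35 × 0.65 + 0.15 × 0.85)]² / 0.20² = (1.200 + 0.764)² / 0.04 = 96.4, so 97 per arm and 194 in total.
- Power at 100 per arm is 91.0%.
- Reading the 20% as relative (35% to 28%) would need 924 per arm, so the authors meant an absolute difference.

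The arithmetic is sound, and the power belongs to a test of two proportions.

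**3. What the stated t-test can detect.** The standard error of the difference is 313 × √(2/100) = 44.3 ml.

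- By the normal approximation, the difference detectable with 90% power is (1.960 + 1.282) × 44.3 = 143 ml.
- With the t distribution it is 0.461 × 313 = 144 ml.
- 144/184 = 78% of the mean.

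**4. Power at assumed differences, 100 per arm.**

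| Assumed reduction in mean | SD 313 in both arms | SD falls in proportion in the lower arm |
|---|---|---|
| One third (184/3 = 61.3, about 62 ml) | about 29% | about 37% |
| One half (92 ml) | about 54% | about 74% |

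In the last column the lower-arm SD is 313 × 2/3 = 208.7 ml or 313/2 = 156.5 ml. For the halving, for example, the standard error is √[(313² + 156.5²)/100] = 35.0 ml, and 92/35.0 = 2.63.

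**5. Does the 20-point target translate into a mean difference?** Under the protocol's own normal model with constant SD, moving from 35% to 15% above 300 ml needs a shift of (1.036 − 0.385) × 313 = 204 ml. The t-test would have over 99% power for that. But the lower arm's mean would be 300 − 1.036 × 313 = −24 ml, which blood loss cannot take. The target therefore gives no usable mean difference.

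**6. The normal model behind the 35%.** It puts Φ(−184/313) = Φ(−0.588) = 28% of losses below zero. As an assumed alternative, take a lognormal with the same mean and SD:

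- σ² = ln[1 + (313/184)²] = 1.359, so σ = 1.166
- μ = ln 184 − 1.359/2 = 4.535
- the proportion above 300 ml is the upper tail at (ln 300 − 4.535)/1.166 = 1.00, about 16%

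A 20-point absolute reduction from 16% is not possible.

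**The case against.** Four points can be made for the plan.

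- **Blood loss is a listed primary outcome.** This is correct. Only the dichotomised form and its threshold are missing.
- **The analysis section is three sentences in a condensed article.** It speaks of tests used when appropriate, and the outcome list includes counts for which a t-test is plainly unsuitable, so an unseen analysis plan may supply a test of proportions. This has some force: a reader might infer that the proportion will never be tested, and the article does not establish that. It does not remove the point, because the article is not silent. It gives one form of summary for all data and two tests, both of means, and that text conflicts with its own basis for the sample size.
- **Low power does not follow from the mismatch.** A reader might infer from the table that the trial is underpowered. The document does not support that. It fixes no mean difference, the results move materially with the SD assumption, and a large enough shift would be detected.
- **The cut-off is already published.** Using 300 ml later would therefore hardly be a post hoc addition. This stands; what remains open is dropping it.

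**Conclusion.** The point holds as a misalignment of three sections. The stated 90% power applies to a two-proportion comparison at 300 ml and not to the t-test or ANOVA that the article describes; the power for a mean difference is simply unstated. With SD 313 ml and 100 per arm, 90% power requires about 144 ml. At the smaller assumed reductions, power runs from about 29% to 37% (one third) and from about 54% to 74% (one half), depending on whether the SD stays fixed or falls with the mean. These figures illustrate what the reader is not told and are not a finding that the trial is too small. The sample size arithmetic reproduces, but the 35% it starts from rests on a normal model that does not suit these data. The mismatch affects the main comparison and should be corrected before outcome data are seen.

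**What to change.** 1. In Primary Outcomes, name the proportion of women with intraoperative blood loss above 300 ml as the outcome that carries the sample size.
2. In Statistical Analysis, compare that proportion by a test of two proportions, reported as a risk difference with a 95% confidence interval. Make blood loss in millilitres secondary, with a method suited to skewed data.
3. In Sample Size Calculation, replace the Z-score conversion with the proportion above 300 ml actually observed in the earlier study, and restate the power.

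If the sponsor prefers to keep millilitres primary, replace the power statement with the detectable mean difference (about 144 ml at 90% power, SD 313 ml, 100 per arm) and say whether a reduction of 78% of the mean is plausible.

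The cost is rewording three sections and looking up one proportion in the sponsor's own earlier data; no new data collection is needed. If the observed proportion is well below 35%, the target difference and possibly the sample size would have to be reconsidered, which is more than wording.

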### Inclusive Criteria

All the patients must be at least over 18 years.All the patients are diagnosed with cesarean scar pregnancy in the first trimester of gestation by ultrasound followed by the guidelines.The conditions of cesarean scar pregnancy in women are stable without severe vaginal bleeding, and all the patients do not need emergency surgery.All the patients want to terminate their pregnancy.Given written informed consent.

### Exclusive Criteria

Patients with other complications of gynecological diseases, such as gynecological cancers, endometriosis, and uterine myoma.Patients who need emergency surgery due to cesarean scar pregnancy.Patients who are not suitable for ultrasound guided suction curettage.Patients who do not want to receive surgical treatment.

### Participant Enrollment

This randomized clinical trial will be introduced to potential trial participants identified from our routine clinic in our hospital by the principal or associate investigators. All the adverse events will be explained by a senior gynecologist (more than 8 years of experiences) or principal investigator or associate investigator before trial enrollment. In addition, either the principal investigator or associate investigators will be available to be contacted at all times after treatment in case of an adverse event. All the patients will be sequentially enrolled.

### Intervention

Eligible patients will randomly receive ultrasound guided suction curettage with or without pre-operative UAE treatment (**Figure 1**). If there is an emergency such as severe bleeding or uterine rupture during treatment, the patients will receive hysteroscopic and/or laparoscopic resection.

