### Data Collection and Follow-Up

#### Pre-Operation

Data on maternal age, parity, gravida, gestational sac age at diagnosis, the size of sac, and the number of previous cesarean section (including the indications of cesarean section) will be collected. The subtypes of cesarean scar pregnancy (Types 1 and II and III) detected by ultrasound findings following a guideline (16) will be classified. In addition, the QRS score for predicting blood loss will be also calculated based on our recently developed quantitative risk-scoring system (13).

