## Discussion

Interventions for cesarean scar pregnancy could cause a massive intraoperative blood loss due to the highly vascular nature of the site of pregnancy. This consequently results in using UAE as one of the options to prevent intraoperative blood loss in clinical practice. However, a recent retrospective study suggested that UAE may be overused in clinical practice (11). Therefore, in this randomized clinical trial, we primarily aim to evaluate the necessity of UAE as a treatment option for cesarean scar pregnancy in order to control the intraoperative blood loss. We will then retrospectively take into account the subtypes of cesarean scar pregnancy to understand whether the optimal options are dependent on the subtypes of cesarean scar pregnancy.

Pre-assessment on predicting intraoperative blood loss which may be dependent on the size and/or site of the sac and the gestational age will help gynecologists select an optimal option for cesarean scar pregnancy treatment. A recent retrospective study used crossover sign (COS) to predict blood loss in surgical treatment (17), suggesting that the crossover sign (COS) is an independent risk factor for severe blood loss during treatment of cesarean scar pregnancy (18). We also recently developed a risk-scoring system (QRS) to estimate blood loss during surgical treatment with a 93.8% sensitivity and 6.3% false negative (13), which has some similarities with the COS system. Due to the relatively small sample size in our previous study, therefore, in this randomized clinical trial with a relatively large sample size, we will retrospectively validate the role of the QRS score in estimating intraoperative blood loss. We hope that this study will generate sufficient evidence for optimal cesarean scar pregnancy treatment. If effective, we believe the QRS score can be a cost-effective and safe tool to estimate intraoperative blood loss in order to reduce the unnecessary use of UAE in clinical practice.

In addition, whether recurrent cesarean scar pregnancy and the outcomes in a subsequent pregnancy including complications,and subsequent fertility in women treated for cesarean scar pregnancy are associated with their previous treatment has not been described well in literature. We hope that the secondary outcomes of the study can provide some useful information on the outcomes of a subsequent pregnancy.

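### No stratification factor is named, and subtype and QRS score enter only retrospectively, although both are known before operation: an avoidable but modest loss of precision

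*Protocol article*

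**What the plan says.** **Allocation.** The Intervention section says: "Eligible patients will randomly receive ultrasound guided suction curettage with or without pre-operative UAE treatment". The Sample Size Calculation section adds that the 200 women are "equally divided into two groups". That fixes the ratio but not the method. No stratification, blocking or minimisation factor appears in the text shown, and the flow chart (Figure 1) is not reproduced.

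**When the two factors are known.** The Pre-Operation section has "The subtypes of cesarean scar pregnancy (Types 1 and II and III) detected by ultrasound findings" classified, and the QRS calculated, before surgery. The abstract says the same.

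**Why they matter to the trial.** The Introduction names gestational age and blood flow around the sac, the two components of the QRS, as risk factors for intraoperative blood loss, and treats a total above three as the at-risk range. The Discussion wants to learn whether the best option differs by subtype.

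**How they are used.** The Primary Outcomes section lists "Retrospectively analyze the intraoperative blood loss, taking into account the subtypes of cesarean scar pregnancy", and beside it the retrospective validation of the QRS as a predictor. The Discussion repeats: "We will then retrospectively take into account the subtypes of cesarean scar pregnancy". The Statistical Analysis section names only a t-test or ANOVA for comparisons.

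**The concern.** Two baseline factors are available before the arm need be released. One is built from stated predictors of the outcome on which the trial is sized, and the other defines a treatment question the trial wants to answer. As described, neither plays a part in allocation, and both are brought in after the fact.

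Two consequences follow if allocation is indeed unstratified:

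- Equal arms overall do not guarantee equal arms within a subtype. A small subtype may be split unevenly, which makes its estimate less precise.
- The share of high-QRS women may differ between arms by chance, which adds noise to a blood-loss comparison made without adjustment.

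Calling the subtype analysis retrospective while listing it as a primary outcome also leaves it open when and how that analysis is fixed.

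**Working it through.** **1. The plan's own sample size.** Inputs from Sample Size Calculation and Statistical Analysis: 35% of women losing more than 300 ml, a 20-point difference (35% vs 15%), "With 90% power at the 5% significance level", two-sided. The 35% rests on a mean of 184 ml and SD of 313 ml; the normal tail above 300 ml is 35.5%, which agrees. The pooled two-proportion formula without continuity correction gives 97 per arm, 194 in total. At 100 per arm, power is 91.0%. The stated 200 reproduces, and stratifying does not change it.

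**2. Chance splits within a subtype.** Subtype shares are not in the document, so the size m is an assumption. With 100 of 200 women in each arm and no stratification, the number of a subtype's m women in one arm is hypergeometric (200, m, 100).

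| Assumed m | Split | Chance of that split or worse, either direction |
|---|---|---|
| 10 | 7:3 | 33.1% |
| 20 | 13:7 | 23.8% |
| 20 | 14:6 | 9.7% |

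The chance of 60:40 or worse is 48% at m = 20, 22% at m = 40, 4% at m = 67 and 0.7% at m = 100. Marked imbalance is therefore a small-subtype problem.

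**3. What an uneven split costs.** With equal variances, a split with fraction f in one arm inflates the variance of the difference by 1/[4f(1−f)]:

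- 13:7 gives 1/(4 × 0.65 × 0.35) = 1.10.
- 14:6 or 7:3 gives 1/(4 × 0.7 × 0.3) = 1.19.

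Within-subtype power for 35% vs 15%, by the same pooled formula, with an even split and with the unfavourable end of the 95% range of splits (more women in the higher-risk arm):

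| m | Even split | Unfavourable split | Loss |
|---|---|---|---|
| 20 | 17% | 11% (14:6) | 6 points |
| 40 | 30% | 25% (26:14) | 6 points (30.4 − 24.6) |
| 67 | 47% | 43% (40:27) | 4 points |
| 100 | 64% | 62% (57:43) | 2 points |

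At m = 20, a 13:7 split in the unfavourable direction gives 13%, a loss of 4 points. A split in the other direction costs no power by this formula (19% at 6:14), so these are losses on the bad side only.

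**4. QRS and the main comparison.** The share scoring above three is not given. Assume 30%, or 60 women. The count in one arm has variance 60 × ½ × ½ × (140/199) = 10.55, so SD 3.25. The share difference between arms has SD 2 × 3.25 = 6.5 points, with a 95% range of about ±12.7. A 36:24 or worse split, a 12-point difference in share, has an 8.9% chance. The resulting shift in the arm difference is 12 points × the risk gap between QRS levels:

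- gap of 20 points: 2.4 points
- gap of 30 points (for example 40% vs 10%): 3.6 points
- gap of 40 points: 4.8 points

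All three gaps are assumptions. The standard error of the arm difference is √(0.35 × 0.65/100 + 0.15 × 0.85/100) = 0.0596, about 6 points. A 3.6-point shift is thus about 0.6 of a standard error, against a target difference of 20 points.

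**The case against.** **The text is silent, not explicit.** A reader might infer that the trial definitely ignores subtype and QRS when allocating. The document does not say so: a random split into equal groups does not exclude stratification, the article is condensed, and Figure 1 is not shown. This stands. The point rests on what is named and on the repeated description of the two factors as retrospective, which is hard to read as describing stratification factors but does not settle the matter.

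**Validating the QRS does not need balance.** A reader might infer that the QRS validation depends on how the arms happen to split. It does not. The listed outcome tests the score as a predictor of blood loss, and no comparison of the arms by QRS level is planned. The hope that the score may one day reduce unnecessary UAE is not such a plan. This stands; the case for including QRS rests only on its prognostic value in the main comparison.

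**Imbalance is not bias and can be handled by analysis.** A reader might infer that an uneven split ruins a subtype estimate beyond repair. Under simple randomisation the within-subtype comparison stays unbiased, the standard error already reflects the realised split, and adjustment deals with prognostic imbalance. This stands. Adjustment cannot add women to the thin arm of a small subtype, but the loss there is limited.

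**The assumed QRS risks fit the plan poorly.** Risks of 40% and 10% with a 30% high-score share imply 0.3 × 40 + 0.7 × 10 = 19% overall, against 25% averaged over the planned 35% and 15%. This is fair. The shift is illustrative, which is why a range is shown.

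**Stratifying or adjusting is a legitimate choice at 200 women.** True, but the article describes neither: the only arm analysis it names is unadjusted, and the subtype analysis is called retrospective.

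**Conclusion.** The point holds as a worthwhile, inexpensive improvement, not as a flaw in validity. The text shown names no stratification factor and makes retrospective use of two factors that are known before operation and matter to its own aims.

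The avoidable loss is modest: at the unfavourable end of the 95% range of splits, about 2 to 6 points of within-subtype power for subtypes of 100 down to 20 women, and a possible shift of a few points in the unadjusted main comparison. The main limit on subtype conclusions is subtype size. Even with perfect balance, power is 17% to 64% over that range, and stratification does not change this.

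These figures assume 100 women per arm, no stratification, subtype sizes of 10 to 100, the planning rates of 35% and 15% within each subtype, and a 30% share with QRS above three. None of the subtype or QRS shares comes from the document. The overall sample size of 200 is unaffected.

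**What to change.** - **Intervention section:** state that allocation is stratified by subtype (I / II / III) and QRS (≤3 / >3), with randomly varying block sizes. Two factors give six strata, about 33 women each on average (200/6), and a rare subtype would hold far fewer. If strata would be sparse, use minimisation on both factors instead. Record both on the allocation form before the arm is released. If allocation is already stratified, one sentence saying so is enough.
- **Abstract, Primary Outcomes, Statistical Analysis and Discussion:** replace the retrospective wording for subtype with a pre-specified analysis that adjusts the blood-loss comparison for subtype and QRS and estimates the UAE effect by subtype with confidence intervals. Describe the QRS validation as pre-specified too, and keep it separate from the arm comparison.
- **Discussion:** say that subtype numbers will limit what can be concluded about each subtype.

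Cost: a new allocation list, two form fields, and arm totals that may differ from 100:100 by a few women. No extra patients, scans or staff are needed.
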